## Abstract

**Background:**

No ideal blood pressure (BP) range has been scientifically determined for acute stroke, and no studies on BP management have been carried out for patients with severe stroke. This trial aims to investigate whether individualized lowering of elevated BP would improve the outcome in patients with severe stroke.

**Methods/design:**

The CHASE trial is a multicenter, randomized, controlled study. A total of 500 adult patients with acute severe stroke will be enrolled in 18 study sites in China and randomized to individualized BP lowering (10–15% reduction from admission level) or guideline-recommended BP lowering. The primary outcome measurement is the proportion of participants with a poor outcome (modified Rankin Scale ≥ 3) at day 90 of enrollment. Secondary outcomes include disability at hospital discharge and the ability of activities of daily living at day 90 of enrollment. The relationship between intervention and the primary outcome will be analyzed using multivariate logistic regression adjusted for study site, demographics, and baseline characteristics.

**Discussion:**

The CHASE trial will be the first study to explore the optimum BP management for acute severe stroke. This trial potentially offers a strong argument for individualized target for lowering elevated BP in patients with severe stroke.

**Trial registration:**

ClinicalTrials.gov, NCT02982655. Registered on 30 November 2016.

**Electronic supplementary material:**

The online version of this article (10.1186/s13063-018-2530-x) contains supplementary material, which is available to authorized users.

## Background

Elevated blood pressure (BP) is one of the most common clinical manifestations in acute stroke; 70–84% [1–3] of stroke patients have a systolic blood pressure (SBP) > 140 mmHg on admission. Despite efforts by a few multicenter studies, the optimum management of BP in acute stroke is still an ongoing dilemma. The ACCESS study and CHHIPS study indicated that modest BP reduction brought down the mortality and the number of vascular events [4], whereas the SCAST study suggested that a careful BP-lowering treatment was associated with a higher risk of poor outcome. The results from the COSSACS study, CATIS study, ATACH-2 study, and INTERACT2 study are neutral: intensive lowering of BP did not reduce the mortality or severe disability significantly [5–8].

However, none of the above studies were targeted at patients with severe stroke. Acute severe strokes account for 13–24% of all strokes [9, 10] and are associated with cerebral hernia, acute cardiac failure [11], systemic complications [12], and death. Given the paucity, we initiated a multicenter randomized controlled trial (RCT) called CHASE, dedicated to test whether individualized antihypertensive treatment would lower the mortality and major disability in patients with severe stroke.

## Methods

### Study objectives

The study aims at assessing the effect of individualized BP-lowering regimens vs guideline-recommended BP-lowering regimens on mortality and morbidity in patients with acute severe stroke.

### Study design

This study has a multicenter, randomized, controlled, single-blind design. Patients will be randomized to two different arms: (1) intervention group (individualized BP lowering), with an individualized target for BP lowering during the first week of hospitalization; and (2) control group (guideline-recommended BP lowering), with a fixed target recommended by the guideline for BP lowering during the first week of hospitalization. The participants are blind to the grouping results; the researchers are informed of the grouping results because they have to follow a specified strategy of BP management. Figure 1 shows a flowchart of the study design. Recommendations for Interventional Trials (SPIRIT) Figure are outlined in Additional file 1.

**Fig. 1 Fig1:**
[figure not shown]
*Flowchart* of participants in the CHASE trial. BP blood pressure, GCS Glasgow Coma Scale, NIHSS National Institute of Health stroke scale, SBP systolic blood pressure

### Study sites

This is a Chinese multicenter trial involving 18 tertiary and district general hospitals in Shaanxi province, an administrative region with a population of 38 million located at the very center of China. The study will be conducted according to Good Clinical Practice guidelines and the Declaration of Helsinki. The study has been approved by the ethics committees of Xijing hospital (KY20162085-2).

### Training of investigators

All CHASE investigators are required to be trained in the protocol, Good Clinical Practice, and use of the Glasgow Coma Scale (GCS), National Institute of Health stroke scale (NIHSS), Barthel index, and modified Rankin Scale (mRS) if they had no recent certifications.

### Study population

The study will include patients with acute severe stroke who have elevated BP on admission. In order to be eligible for inclusion in the study, the patients have to comply with the following criteria: (1) age ≥ 18 years; (2) the randomly assigned BP-lowering regimen is able to be commenced within 72 h after the onset of stroke (ischemic or hemorrhagic), confirmed by a computed tomography (CT) or magnetic resonance imaging (MRI) scan of the brain (if the precise timing of the onset of symptoms or signs of the qualifying event is unknown, then the time of onset will be taken as the last time the patient was known to be well); (3) GCS on admission ≤ 12 or NIHSS on admission ≥ 11; (4) there are at least two SBP measurements of ≥ 150 and ≤ 210 mmHg, recorded ≥ 5 min apart (patients with an initial SBP < 150 mmHg may be randomized when the SBP fulfils entry criteria on rechecking up to 72 h after the onset of stroke); and (5) written informed consent is able to be obtained directly from the patient or an appropriate surrogate, based on local ethics committee recommendations.

Exclusion criteria are: (1) patients who have received thrombolytic therapy, embolectomy, or decompressive craniectomy for the current stroke; (2) patients with subarachnoid hemorrhage; (3) known definite contraindication to acute BP lowering (e.g. known severe carotid, vertebral, or cerebral arterial stenosis, Moyamoya disease or Takayasu’s arteritis, high grade stenotic valvular heart disease); (4) secondary to a structural abnormality in the brain (e.g. an arteriovenous malformation, intracranial aneurysm, tumor, or trauma); (5) unstable vital signs and requiring the use of vasoactive agents; (6) known existing dementia or pre-stroke disability (e.g. score 3–5 on the modified Rankin scale); (7) concomitant medical illness that would interfere with the outcome assessments and/or follow-up (advanced cancer; severe pulmonary dysfunction [forced expiratory volume in 1 s < 50%]; severe cardiac dysfunction [ejection fraction ≤ 50%]; severe hepatic failure [Child-Pugh score ≥ 7]; severe renal failure [glomerular filtration rate ≤ 30 mL/min or serum creatinine ≥ 4 mg/dL]); (8) patients who are currently participating in other investigational trials; and (9) patients who are considered to have a high likelihood of not adhering to the study treatment or the follow-up regimen.

### Randomization

A secure website (http://traillogin.applinzi.com) will be used to perform the centralized randomization (computerized random numbers). Patients will be randomized into one of the two intervention arms (1:1).

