### Trial interventions

In patients who are assigned to receive individualized regimen to lower BP (individualized BP-lowering group), antihypertensive treatments are to be initiated to reduce SBP to a range of 130–180 mmHg and by 10–15% from the admission level within 2 h after randomization. SBP in the individualized BP-lowering group is to be maintained around the target level for one week with or without the use of hypertensive agents. In participants who were assigned to receive guideline-recommended treatment [13, 14] (guideline-recommended BP-lowering group), antihypertensive agents are to be administered if the SBP was > 200 mmHg in acute ischemic stroke (AIS) or the SBP was > 180 mmHg in intracerebral hemorrhage (ICH). The goal is to maintain the SBP < 200 mmHg in ischemic stroke and < 180 mmHg in ICH for one week with or without the use of hypertensive agents. Table 1 presents the detailed management of BP in the first week after randomization.

**Table 1 Tab1:** Management of BP during the first week after randomization

SBP level	Approaches
*Individualized BP-lowering group*	
Above the range^a^	Increase the dose of AHD or use other stronger AHDs
In the range^a^	Maintain the regimen
Below the range^a^ and > 100 mmHg	Reduce the dose of AHD or withdraw AHD
< 100 mmHg	Use vasopressor agents
*Guideline-recommended BP lowering-group*	
> 200 mmHg in AIS > 180 mmHg in ICH	Increase the dose of AHD or use other stronger AHDs
< 200 and > 100 mmHg in AIS < 180 and > 100 mmHg in ICH	Use the least dose of AHD to keep SBP not > 200 mmHg in AIS, 180 mmHg in ICH
< 100 mmHg	Use vasopressor agents

^a^10–15% reduction from admission level and in the range of 130–180 mmHg

*AHD* antihypertensive drug, *AIS* Acute ischemic stroke, *BP* blood pressure, *ICH* intracerebral hemorrhage, *SBP* systolic blood pressure

The selection of antihypertensive agents is based on the local availability; no specific agent is stipulated (both intravenous and oral agents can be used). Patients who take antihypertensive agents before stroke continue to take the same antihypertensive medication (same drug with same dosage). The rest of the medical care for stroke is based on the guideline [15, 16]. The management of BP after the first week of hospitalization adheres to the guideline as well.

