### Study procedures

Table 2 presents all the variables measured at each time point of the study. At the time point of baseline screening, demographics, subtypes of stroke, medical history (e.g. AIS, ICH, coronary event, diabetes mellitus, and hypertension), physical examination, clinical scores (NIHSS, GCS, Barthel index, mRS), and vital signs are recorded. On day 1 and day 7, routine laboratory tests for stroke patients are assessed, including blood routine, liver and renal function test, serum lipid, fasting glucose, urine routine, and electrocardiography. Co-morbidities on the day of screening and hospital discharge are recorded. Clinical scores on day 7, the day of hospital discharge, and day 90 are collected. During the whole hospitalization, BP, vital signs, and adverse events (AEs) are monitored, and concomitant treatments are documented.

**Table 2 Tab2:** Timing and content of study assessments

Items	Day of enrollment									
	Screening	1	2	3	4	5	6	7	HD	90
Written informed consent	●									
Inclusion and exclusion criteria	●									
Demographics	●									
Medical history	●									
Physical examination	●							●	●	
BP monitoring	●	●	●	●	●	●	●	●	●	
Laboratory tests		●						●		
NIHSS and GCS	●								●	
Barthel index and mRS	●								●	●
Vital signs monitoring	●	●	●	●	●	●	●	●	●	
Co-morbidities	●								●	
AEs		●	●	●	●	●	●	●	●	
Use of antihypertensive agents		●	●	●	●	●	●	●	●	
Concomitant therapies		●	●	●	●	●	●	●	●	

*HD* hospital discharge, *BP* blood pressure, *GCS* Glasgow Coma Scale, *NIHSS* National Institute of Health stroke scale, *mRS* modified Rankin Scale, *AE* adverse event

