### Statistical and analytical plan

Patients will be analyzed according to the intention-to-treat principle. Analyses will be conducted at the Shaanxi Cerebrovascular Disease Clinical Research Center by blinded biostatisticians. Baseline characteristics will be summarized using univariate analyses. Categorical variables will be presented as the number and percent, whereas the continuous variables will be presented as mean (± standard deviation) or median (interquartile range). We will compare the proportions for the primary and secondary outcomes between patients randomized to the individualized BP-lowering group vs the guideline-recommended BP-lowering group using the Chi-square test. We will calculate the relative risk reduction, absolute risk reduction, and the number needed to treat with individualized BP-lowering target to prevent one death. Logistic multivariate analyses will be used to adjust for potential confounding effects of different variables and estimate adjusted odds ratios and associated 95% confidential intervals. Two-sided *p* values ≤ 0.05 will be considered significant. Statistical analysis will be performed with SPSS version 22 software (SPSS Inc., Chicago, IL, USA).

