## Discussion

A few multicenter, randomized studies have been carried out to search for the ideal BP range for patients with acute stroke; however, none of them aimed at severe stroke, which has a much higher rate of mortality and disability. No clinical evidence can be used to guide the BP management in critical care for those stroke patients with an initial presentation of severe neurological deficits. Our study aims to test the superiority of individualized BP lowering compared to guideline-recommended BP lowering in improving three-month outcome. Our study will provide the first evidence on the optimum BP-lowering target for patients with acute severe stroke.

Factors that contribute to raised BP in acute stroke are multifaceted, such as history of hypertension, stroke severity, pressure response to hospital admission, infarct area related to BP adjustment, and increased intracranial pressure [19]. Raised BP later falls into the following types: without antihypertensive medications BP declines spontaneously; with antihypertensive medications BP does not decline, declines modestly (10–15% from baseline), or intensively (≥ 20% from baseline value) [20]. Elevated BP raises the risk of cerebral edema, hemorrhagic transformation of the infarct [21], hematoma expansion [22], cardiac complications, and renal insufficiency. On the other hand, a decrease in BP might reduce the blood perfusion of the brain and aggravate the cerebral ischemic injury, especially in large territorial ischemia [23]. One clinical study indicated that both large increase and reduction in BP (> 20 mmHg) were associated with a higher risk of early neurological deterioration, increased infarct volume, and poorer outcome at three months [24]. Therefore, a proper management of BP is essential for stroke patients.

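### The control SBP goal depends on stroke type but the individualized target does not, so the planned contrast nearly vanishes in ICH admitted at 200–210 mmHg and the pooled chi-square test mixes unequal contrasts

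*Protocol article*

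**What the plan says.** All references are to the Protocol article.

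- **Study population.** One entry range serves both stroke types: "there are at least two SBP measurements of ≥ 150 and ≤ 210 mmHg, recorded ≥ 5 min apart".
- **Trial interventions, individualized arm.** Treatment is to "reduce SBP to a range of 130–180 mmHg and by 10–15% from the admission level within 2 h after randomization". Stroke type plays no part. Under Table 1, drug is reduced or withdrawn if SBP falls below this range.
- **Trial interventions, control arm.** "The goal is to maintain the SBP < 200 mmHg in ischemic stroke and < 180 mmHg in ICH for one week". Table 1 asks for the smallest drug dose that keeps SBP under the type-specific threshold, and sets no further action level until 100 mmHg.
- **Randomization.** Allocation is central and computerized: "Patients will be randomized into one of the two intervention arms (1:1". No stratification factor is named.
- **Study procedures.** The baseline record includes "subtypes of stroke".
- **Statistical and analytical plan.** The arms are compared as a whole "using the Chi-square test". The Abstract adds "multivariate logistic regression adjusted for study site, demographics, and baseline characteristics". Neither place names stroke type.

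**The concern.** Stroke type decides which control regimen a patient receives, so it is part of the definition of the comparison and more than an ordinary prognostic covariate. The entry range runs up to 210 mmHg. In ICH the control ceiling (180) coincides with the upper cap of the individualized range (180), so at high admission pressures the two arms can be aiming at almost the same SBP. In AIS the control ceiling is 20 mmHg higher and the arms stay apart.

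A single pooled comparison then averages patients with a real planned contrast and patients with almost none. If the trial ends with no difference, a reader cannot tell whether individualized lowering has no effect or whether part of the sample was never treated differently.

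**Working it through.** The article states no planned separation between arms, so there is no figure of its own to reproduce on that. It can be derived from the stated targets.

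**1. Inputs.** Let S be the admission SBP, 150–210 mmHg (Study population). The calculation takes admission SBP to lie within the entry range; the article lets patients first below 150 mmHg qualify on rechecking.

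- Individualized range: from max(0.85·S, 130) to min(0.90·S, 180).
- Control level in ICH: min(S, 180). Control level in AIS: min(S, 200).
- Assumption: a control patient below the threshold stays at S, and one above it is brought just to the threshold.

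**2. Gap = control level − midpoint of the individualized range (mmHg).**

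| S | Individualized range | Midpoint | Gap in ICH | Gap in AIS |
|---|---|---|---|---|
| 150 | 130–135 | 132.5 | 17.5 | 17.5 |
| 180 | 153–162 | 157.5 | 22.5 | 22.5 |
| 190 | 161.5–171 | 166.25 | 13.8 | 23.8 |
| 200 | 170–180 | 175 | 5.0 | 25.0 |
| 210 | 178.5–180 | 179.25 | 0.8 | 20.8 |

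From 150 to 180 mmHg the two types are identical. Above 180 they part. From the upper end of the individualized range, the gap at 200 and 210 mmHg is 180 − 180 = 0 in ICH and 200 − 180 = 20 in AIS.

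**3. Reduction an ICH control needs in order to reach 180 mmHg.** At 200: 1 − 180/200 = 10.0%. At 210: 1 − 180/210 = 14.3%. Both lie inside the intervention's own 10–15% band.

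**4. Size of the dilution.** If a share f of all patients has no effective contrast and the rest have the planned 6-point effect, the pooled effect is 6·(1 − f). The documents do not give f. Assumed values of 5%, 10% and 20% give 5.7, 5.4 and 4.8 points.

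**5. What an interaction test could show at N = 500.** Assume an ICH share of 30–70% and opposite 6-point effects around 60% (54% in AIS, 66% in ICH, individualized arm). With n_A and n_I patients per arm,

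SE = √[(0.60·0.40 + 0.54·0.46)/n_A + (0.60·0.40 + 0.66·0.34)/n_I], and power = Φ(0.12/SE − 1.96).

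At a 50% share, n_A = n_I = 125, SE = 0.0873 and power is 28%. At 30% ICH (175 and 75) SE = 0.0948 and power is 24%. Over the whole assumed range power is 24–28%. Power to detect 60% against 54% within one type is 11–20%.

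As a separate matter, the stated power of at least 80% for 60% against 54% does not reproduce: 250 per arm gives about 27%. The present point does not depend on that, but it is a further reason to treat results by type as supportive.

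**The case against.** **This is a condensed article.** It does not say that randomization is unstratified or that no analysis by type exists, and either may sit in a fuller document. That stands, and the missing subgroup analysis is not itself the finding. The adjusted model also covers baseline characteristics, and stroke type is recorded at baseline, so adjustment may already be intended. What remains is what the article does state: targets that overlap in ICH at high admission SBP, and a chi-square comparison of whole arms.

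**The problem is confined to part of the sample.** That also stands. The planned contrast is the same in both types up to 180 mmHg, and the number of ICH patients at 200–210 mmHg is unknown.

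**Opposite effects by type.** A reader might infer that pooling hides benefit in one type and harm in the other. The documents do not support more than the possibility. A shrinking contrast only pulls the effect toward zero. The Discussion does warn that "a decrease in BP might reduce the blood perfusion of the brain and aggravate the cerebral ischemic injury", but it also lists cerebral edema and hemorrhagic transformation of the infarct as harms of high pressure, so mechanisms for benefit exist in AIS too. The preliminary data point the same way in both types, although they are retrospective, were not significant in ICH, and compare reductions above and below 15% rather than the two trial regimens.

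**Bias from simple randomization.** A reader might infer this as well. Unstratified allocation is unbiased. It allows chance imbalance: with an assumed ICH share of 30–70%, a between-arm difference above 5 points has probability 22–26%. The standard error of the unadjusted test already reflects that.

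**Control treated harder than intervention.** In ICH at 210 mmHg, a control SBP below 178.5 would lie under the individualized range. The smallest-dose instruction works against overshoot, so the text supports overlap but not a planned reversal.

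**Conclusion.** The point holds in a limited form. In ICH admitted at about 200–210 mmHg the stated targets leave a planned separation of 5.0 falling to 0.8 mmHg, against 25.0 to 20.8 mmHg in AIS. At 150–180 mmHg there is no difference between types. The pooled chi-square test therefore averages unequal contrasts, which dilutes the effect and clouds a null result.

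The range arithmetic rests only on the stated targets. The gaps also assume that untreated controls stay at admission SBP. Spontaneous decline, or continued pre-stroke medication, would change the achieved separation. How much the pooled estimate is diluted cannot be determined, because the share of ICH patients in the affected band is not given.

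**What to change.** 1. **Reconcile the targets.** In Trial interventions and Table 1, reconcile the overlapping ICH targets at high admission SBP with the intended contrast, or state that little separation is expected there. Which target is right is a clinical matter that this review does not decide.
2. **Primary comparison.** Name stroke type (AIS/ICH) as an adjustment or stratification factor in the primary analysis. It is already collected, so the cost is a line of analysis text.
3. **By-type results.** Prespecify the treatment effect within each type and the treatment-by-type interaction. Report achieved SBP separation by arm within each type and by admission SBP (≤ 180 vs > 180 mmHg). A null result can then be read as absent effect or absent contrast. Label these results supportive. The drawback is the low interaction power shown above.
4. **No rule based on signs.** Do not withhold the pooled estimate merely because the two types point in opposite directions. With a uniform 60% against 54% effect and 40% ICH (assumed), the chance of a wrong-direction estimate is about 14.7% in AIS (Φ(−0.06/0.0571), 150 per arm) and 19.5% in ICH (Φ(−0.06/0.0699), 100 per arm). Opposite signs then occur with probability 0.147 × 0.805 + 0.853 × 0.195 ≈ 28%.
5. **Optional.** Stratify the remaining randomizations by type. Recruitment has started (Trial status), and such a change would need agreement and ethics approval (Protocol amendments), so the gain is debatable. The sample size would not change.

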### Trial interventions

In patients who are assigned to receive individualized regimen to lower BP (individualized BP-lowering group), antihypertensive treatments are to be initiated to reduce SBP to a range of 130–180 mmHg and by 10–15% from the admission level within 2 h after randomization. SBP in the individualized BP-lowering group is to be maintained around the target level for one week with or without the use of hypertensive agents. In participants who were assigned to receive guideline-recommended treatment [13, 14] (guideline-recommended BP-lowering group), antihypertensive agents are to be administered if the SBP was > 200 mmHg in acute ischemic stroke (AIS) or the SBP was > 180 mmHg in intracerebral hemorrhage (ICH). The goal is to maintain the SBP < 200 mmHg in ischemic stroke and < 180 mmHg in ICH for one week with or without the use of hypertensive agents. Table 1 presents the detailed management of BP in the first week after randomization.

**Table 1 Tab1:** Management of BP during the first week after randomization

SBP level	Approaches
*Individualized BP-lowering group*	
Above the range^a^	Increase the dose of AHD or use other stronger AHDs
In the range^a^	Maintain the regimen
Below the range^a^ and > 100 mmHg	Reduce the dose of AHD or withdraw AHD
< 100 mmHg	Use vasopressor agents
*Guideline-recommended BP lowering-group*	
> 200 mmHg in AIS > 180 mmHg in ICH	Increase the dose of AHD or use other stronger AHDs
< 200 and > 100 mmHg in AIS < 180 and > 100 mmHg in ICH	Use the least dose of AHD to keep SBP not > 200 mmHg in AIS, 180 mmHg in ICH
< 100 mmHg	Use vasopressor agents

^a^10–15% reduction from admission level and in the range of 130–180 mmHg

*AHD* antihypertensive drug, *AIS* Acute ischemic stroke, *BP* blood pressure, *ICH* intracerebral hemorrhage, *SBP* systolic blood pressure

The selection of antihypertensive agents is based on the local availability; no specific agent is stipulated (both intravenous and oral agents can be used). Patients who take antihypertensive agents before stroke continue to take the same antihypertensive medication (same drug with same dosage). The rest of the medical care for stroke is based on the guideline [15, 16]. The management of BP after the first week of hospitalization adheres to the guideline as well.

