However, no ideal BP range has been scientifically determined yet. Guidelines for AIS from the American Heart Association (AHA)/American Stroke Association suggest that BP targets are based on best clinical judgment and a reasonable estimate might be to lower the SBP by 15% if the BP is > 220/120 mmHg [15]. For ICH patients presenting with SBP < 180 mmHg, guidelines from AHA in 1999 suggest to defer antihypertensive therapy; guidelines from AHA in 2015 suggest to lower SBP to 140 mmHg. Chinese guidelines for AIS recommend the use of hypertensive therapy when SBP is > 200 mmHg [14]. Also, Chinese guidelines for ICH suggest that antihypertensive therapy should be initiated when SBP is > 180 mmHg and a target around 160/90 mmHg can be considered although evidence is lacking [25]. None of the above guidelines mentioned any BP-lowering regimen specifically for severe stroke due to the lack of clinical evidence.

Given the paucity of studies on BP management for severe stroke, we performed a retrospective preliminary study in stroke patients admitted to neurological intensive care unit (NICU) in Xijing Hospital (a tertiary teaching hospital) in the last three years and found that NICU mortality was significantly higher in patients with SBP reduced by > 15% than those with SBP reduced by < 15%. This difference of mortality remained significant in patients with AIS. For ICH, the NICU mortality was also higher in patients with SBP reduced by > 15% than those with SBP reduced by < 15%, albeit insignificant.

Based on the above result and previous studies, we designed a multicenter RCT to investigate whether individualized lowering (10–15% reduction from admission level) of elevated BP would improve the outcomes in patients with severe stroke, hoping to provide evidence of BP management for acute severe stroke, help improve the quality of life, and reduce family and social burdens.

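### For eligible patients whose initial SBP was below 144.4 mmHg, the individualized target is empty if read literally: it is tied to admission SBP, but entry may rest on a later reading

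*Protocol article*

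**What the plan says.** The Trial interventions section of the protocol article sets the individualized arm's task: SBP is to be brought inside 130–180 mmHg "and by 10–15% from the admission level within" 2 h of randomization. Footnote a of Table 1, which governs titration through the first week, repeats both conditions jointly: "10–15% reduction from admission level and in the range of 130–180 mmHg".

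The Study population section opens with "The study will include patients with acute severe stroke who have elevated BP on admission". Inclusion criterion 4 then requires that "there are at least two SBP measurements of ≥ 150 and ≤ 210 mmHg, recorded ≥ 5 min apart", and adds in parentheses that "patients with an initial SBP < 150 mmHg may be randomized when the SBP fulfils entry criteria on rechecking up to 72 h" after onset. It puts no lower limit on that initial SBP.

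The article does not define the admission level, does not move the reference to the qualifying reading, and does not rank the percentage condition against the absolute one. The Discussion gives part of the motivation for the 10–15% figure: in a retrospective single-hospital series, "NICU mortality was significantly higher in patients with SBP reduced by" more than 15% than in those with a smaller reduction.

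**The concern.** The experimental treatment in this trial is the target itself. A target made of two conditions exists only where they overlap. Here one condition moves with the admission SBP and the other is fixed, while eligibility is decided on readings that may come later and differ from the admission SBP.

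If the conditions fail to overlap for some patients, clinicians at different sites may follow different conditions for the same kind of patient, and adherence for those patients cannot be scored against one standard. The sample size section assumes 10% non-adherence, so a scoreable target matters. A reference reading that no longer reflects the pressure being treated can also imply a much larger fall than 10–15% suggests, or no fall at all. Recruitment had started when the article was submitted (Trial status), so such patients may already be enrolled.

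**Working it through.** **Inputs.** Percentage condition: 10–15% below admission SBP, written A. Absolute condition: 130–180 mmHg. Both are from Trial interventions and Table 1 footnote a. Qualifying SBP at entry, written S: 150–210 mmHg. Initial SBP: may be below 150 with no floor. Both are from Study population, criterion 4. The initial SBP is taken as the admission level.

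**Step 1: where the target exists.** The target is the interval from max(0.85A, 130) to min(0.90A, 180). It is non-empty only if 0.90A ≥ 130, so A ≥ 130/0.90 = 144.4, and 0.85A ≤ 180, so A ≤ 180/0.85 = 211.8. The range 150–210 lies wholly inside these limits, so every patient whose admission SBP is itself 150–210 has a target.

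| Admission SBP (mmHg) | 10–15% below | Also within 130–180 |
|---|---|---|
| 130 | 110.5–117 | none |
| 140 | 119–126 | none |
| 145 | 123.25–130.5 | 130–130.5 |
| 149 | 126.65–134.1 | 130–134.1 |
| 150 | 127.5–135 | 130–135 |
| 180 | 153–162 | 153–162 |
| 200 | 170–180 | 170–180 |
| 210 | 178.5–189 | 178.5–180 |

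**Step 2: what Table 1 then instructs.** Take a patient with an initial SBP of 140 who qualifies at 160.
- At 160, the percentage condition (119–126) puts the patient above the range, so treatment is intensified. The absolute condition puts the patient in range, so the regimen is kept.
- At 128, the percentage condition still says above, so intensify. The absolute condition says below, so reduce or withdraw.

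The second case gives opposite orders at the same pressure.

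**Step 3: initial SBP of 144.4–149.9.** A target exists. The smallest fall from the entry pressure that reaches it is (S − 0.90A)/S.
- A = 145 (upper end 130.5): from 150, 19.5/150 = 13.0%; from 180, 49.5/180 = 27.5%; from 210, 79.5/210 = 37.9%.
- A = 149 (upper end 134.1): 10.6%, 25.5% and 36.1% from the same three entry values.
- A = 145 and S = 185: (185 − 130.5)/185 = 29.5% to reach the upper end and (185 − 130)/185 = 29.7% to reach the lower end.

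Measured from admission, the last example is a fall of only 14.5/145 = 10.0% to 15/145 = 10.3%. The size of the fall depends entirely on which reading is the reference.

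**Step 4: the reverse direction.** A patient admitted at 190 has a target of 0.85 × 190 = 161.5 to 0.90 × 190 = 171. If SBP is 155 at randomization, the patient starts below the range in the lowering arm. Table 1 has a row for this, so it is not a contradiction, but it shows the effect of the admission anchor in patients who did not need the recheck clause.

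**Step 5: where the conflict comes from.** If the percentage is computed from the qualifying SBP instead, every value from 150 to 210 gives a non-empty range (rows 150 to 210 above). The empty target therefore comes from combining the admission anchor with the recheck clause. This is a diagnosis, not a recommended rule.

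**The case against.** The strongest reply is that the conflict depends on one reading. The criteria speak of an initial SBP, the intervention text of the admission level, and the Discussion describes a modest decline of 10–15% relative to baseline. If the sponsor means the qualifying SBP, every eligible patient has a target and none needs a fall above 15%. A fuller protocol or the case report form may settle this. The reply has force, but it does not clear the article. The admission anchor is used in the Abstract, in Trial interventions, in Table 1 footnote a and again in the Discussion, and criterion 4 itself separates the initial SBP from the later qualifying one. The article states both rules and they collide.

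Several stronger readings are tempting and should be resisted.
- A reader might infer that the arm as a whole cannot be delivered. It can be: everyone with an admission SBP of 150–210 has a target.
- The Background reports that 70–84% of stroke patients have SBP above 140 on admission, and a reader might take the remaining 16–30% as the share affected. That describes stroke patients in general. The relevant group is severe-stroke patients with a low first reading and later qualifying ones, for whom no count is given.
- A reader might object to very narrow ranges. Narrow is not empty, and the text asks only that SBP be held around the target.
- A reader might point to first readings above 211.8 mmHg. The recheck clause covers only initial SBP below 150, so such patients are not expressly admitted.
- A reader might conclude that the 29–30% example breaches the article's own mortality threshold. The Discussion does not state the reference reading for its 15% cut. The series is also retrospective and from one hospital, and the difference was not significant in ICH.

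**Conclusion.** The text is wrong as written for a subset of patients. On the literal reading, with the initial SBP as the admission level, a patient who enters through the recheck clause with an initial SBP below 144.4 mmHg has no individualized target. Table 1 then gives conflicting titration instructions, and nothing says which condition prevails. For an initial SBP of 144.4–149.9 the target exists but can imply a fall from the pressure at randomization well above 15%. That is a caution about the anchor rather than a proven departure from the article's own evidence. The 190-to-155 case is covered by Table 1 and only illustrates the same anchor.

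The number of patients affected cannot be obtained from the article and may be small. The conclusion does not depend on sample size, alpha or power. It disappears if the sponsor states that the reference is the qualifying SBP.

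**What to change.** Reconcile inclusion criterion 4, the Trial interventions text and Table 1 footnote a, so that one stated reference SBP gives a non-empty target for every eligible patient. State which condition prevails if the two ever disagree. The choice of reference and of clinical rule is for the investigators.

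Record the reference SBP and the computed target range at randomization, so that adherence is scored against a fixed value. Report how many patients already enrolled had no valid target under the present wording.

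The cost is a short protocol amendment, one computed field in the web randomization form, and a count from data already held.
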